## Abstract

An ongoing pragmatic, randomized, unblinded clinical trial compares pimavanserin and quetiapine for psychosis in Lewy body diseases over 6 months (*n* = 60). Relative to local explanatory clinical trials, retention is higher (93% vs 40%, *p* < 0.001) and Hispanic enrollment greater (38% vs 21%, *p* = 0.043), reflecting the clinic demographics. Embedding pragmatic trials within routine care can enhance retention and diversity, thereby improving representativeness and real-world applicability of clinical research. Registry: ClinicalTrials.gov, TRN: NCT05590637; Registration Date: 18 October 2022.

Parkinson’s disease (PD) and dementia with Lewy bodies (DLB), collectively referred to as Lewy body diseases (LBDs), are neurodegenerative diseases that cause both abnormal movement such as tremor and bradykinesia as well as non-motor symptoms, including mood, cognitive, and behavioral problems. Psychosis - which manifests as hallucinations, illusions, delusions, or a false sense of presence or passage^1^ - is a particularly distressing non-motor symptom that worsens quality of life, heightens caregiver strain, and increases hospitalization, institutionalization, and mortality^2–6^.

Research efforts are underway to advance understanding and treatment options in LBDs, though the traditional, explanatory randomized controlled trials (RCTs) that are often used face considerable barriers to patient enrollment and long-term participation. In one survey of 832 individuals with PD, less than 10% had ever participated in a clinical trial, even though most respondents indicated they would be open to doing so^7^. Broader analyses show that about three quarters of investigators fall short of enrollment goals, and more than a quarter of studies close without enrolling any participants^8^. Maintaining participation after enrollment is also difficult, particularly when protocols require frequent visits and demanding procedures, which often depend on caregiver time and resources^9,10^. These barriers are even more pronounced in LBDs, where cognitive impairment complicates adherence, and caregivers carry a large share of the logistical responsibility. In addition, racial and ethnic minority groups continue to be strikingly underrepresented. Across decades of U.S.-based PD RCTs, fewer than 20% have reported participant race, and when they did, non-White individuals comprised only about 8% of enrollees despite representing roughly 20% of the older adult population^11^. More recent reviews show little progress, with over three-quarters of studies still lacking racial and ethnic data and minority enrollment remaining below 5%^12,13^.

Although explanatory RCTs remain central to establishing causality, their rigorous conditions can make results less applicable to routine clinical care and may overlook benefits meaningful to patients^14,15^. These studies emphasize internal validity through blinding, placebo use, narrow eligibility criteria, and extensive assessments. In real world settings, however, treatment response depends on more than the intervention itself. The clinician-patient relationship^16–18^, placebo effects^19,20^, and individual preferences^21,22^ all shape adherence and outcomes. In response, pragmatic clinical trial designs have been proposed as a way to study treatments under conditions that better reflect everyday medical practice^23^.

In this study, we describe a pragmatic randomized trial comparing two antipsychotic treatments, pimavanserin and quetiapine, for psychosis in LBDs over a period of six months. While pimavanserin is the only medication approved by the U.S. Food and Drug Administration specifically for PD psychosis, its real-world use is limited by cost, insurance restrictions, and concerns about its comparative effectiveness. Quetiapine is often prescribed as a more accessible and cost-effective alternative^24,25^. However, existing evidence for quetiapine use in LBDs is mixed, with studies limited by small sample sizes and inconsistent results, further illustrating limitations of explanatory RCTs^26–31^.

By integrating research into standard clinical workflows, this pragmatic trial aims to produce findings that are more applicable to real-world practice in a diverse population. To date, 60 participants (mean age 76 years) have enrolled (Table 1), comprising 43% of patients seen by the enrolling clinicians for this study (*n* = 141), and 25% of all patients (*n* = 239), with PD or DLB who were seen in the University of Texas Health Science Center at San Antonio (UTHSCSA) Neurology Clinic and prescribed quetiapine or pimavanserin during the study period, as identified using SlicerDicer (Epic Systems Corporation, Verona, WI). Thirty (50%) were randomized to receive pimavanserin and 30 (50%) to quetiapine. Of the total cohort, 52 (87%) are diagnosed with PD (including those with PD dementia (PDD)) and 8 (13%) with DLB. Twenty-four (40%) are women and 23 (38%) identify as Hispanic. At the time of this report, a total of 56 participants are enrolled and retained (93%), including 48 who have completed the study and 8 who remain active with a mean time since enrollment of 130 days. Four participants were lost to follow-up (2 due to death and 2 due to relocation or withdrawal). Among the 4 participants lost to follow-up, all are men and White, including 1 who identifies as Hispanic and 1 with unknown ethnicity. Based on ZIP codes, participants have a mean Social Vulnerability Metric (SVM) score of −0.41 (39.7 percentile), where negative SVM scores and lower SVM percentiles indicate less social vulnerability^32^.

**Table 1 Tab1:** Baseline Characteristics of Enrolled Participants

Patient Characteristics	Total = 60
Age, mean ± SD (years)	76 ± 8
Sex, male, *n* (%)	36 (60)
Race, White, *n* (%)	56 (93)
Hispanic Ethnicity, *n* (%)	23 (38)
Social determinants of health	
Primary insurance, *n* (%)	
* Medicare/Medicare Advantage*	46 (77)
* Commercial (including managed care plans)*	12 (20)
* Tricare*	1 (2)
* Uninsured*	1 (2)
Marital status, *n* (%)	
* Married/domestic partnership*	41 (68)
* Single/separated/divorced*	11 (18)
* Widowed*	8 (13)
SVM metric, mean ± SD	-0.41 ± 1.29
SVM percentile, mean ± SD	39.70 (34.60)
Diagnosis, n (%)	
PD	52 (87)
* PD without dementia*	28 (54)
* PD with dementia (PDD)*^a^	24 (46)
DLB	8 (13)
Has DBS, n (%)	5 (8)
Baseline MDS-UPDRS Part III, mean ± SD (points)^b^	49 ± 14
H&Y, mean ± SD (points)^c^	3 ± 1
PD medication use, *n* (%)	
Carbidopa-Levodopa (any formulation)	53 (88)
Amantadine	10 (17)
Dopamine agonist	9 (15)
MAO-B inhibitor	7 (12)
COMT inhibitor	1 (2)
Adenosine A2A receptor antagonist	1 (2)
None	6 (10)
Cholinesterase inhibitor use, n (%)	22 (37)
Symptoms of psychosis, n (%)	
Hallucinations	58 (97)
Delusions	34 (57)
Treatment allocation, *n* (%)	
Pimavanserin	30 (50)
Quetiapine	30 (50)

*SD* standard deviation, *n* number, *SVM* Social Vulnerability Metric, *DBS* deep brain stimulator, *MDS-UPDRS* Movement Disorders Society Modified Unified Parkinson’s Disease Rating Scale, *H&Y* Hoehn and Yahr score, *MAO* Monoamine oxidase inhibitor, *COMT* Catechol-O-Methyltransferase.

^a^ Based on cognitive status documented in the medical record at the time of enrollment, or within 12 months after enrollment if no cognitive status documentation was available at enrollment.

^b^among 57 with data available.

^c^among 54 with data available.

The demographics of the trial cohort were compared both with the overall clinic population of people with PD (PwP) and with those who participated in explanatory RCTs at the trial center. Compared with the broader population of PwP followed in the UTHSCSA Movement Disorders Clinic, there are no significant differences in race, ethnicity, or sex among the trial participants (Table 2). When compared with participants enrolled in concurrent explanatory RCTs for people with PD and/or DLB within the Movement Disorders Division at our center (*n* = 68), this pragmatic trial enrolled a higher percentage of Hispanic participants (38% vs 21%; *p* = 0.043) and demonstrated improved retention (93% vs 40%; *p* < 0.001); there are no differences in sex or race.

**Table 2 Tab2:** Comparison of the trial participant demographics to those of the overall PD clinic cohort

Patient Characteristics	Pragmatic trial participants, *n* = 60	Overall Clinic Cohort of PwP, *n* = 1111	*p*-value
Sex, male, *n* (%)	36 (60)	694 (62)	0.693
Ethnicity, *n* (%)			0.138
Hispanic	23 (38)	337 (30)	
Non-Hispanic	33 (55)	655 (60)	
Unknown	4 (7)	119 (11)	
Race *n* (%)			0.808^a^
White	56 (93)	922 (83)	
Black or African American	1 (2)	13 (1)	
Asian	1 (2)	11 (1)	
More than 1 race	1 (2)	7 (1)	
Unknown/Other	1 (2)	158 (14)	

^a^among patients with race data available.

This brief communication describes a pragmatic trial design for evaluating antipsychotic treatments in LBDs that proved both feasible and effective in achieving strong recruitment, high retention and greater inclusion of diverse participants. The retention rate and minority representation are higher than is typically reported in RCTs^11–13,33,34^, though similar patterns of high retention have been reported in other pragmatic PD trials. For example, in the PD MED study, 91% of the 1620 participants remained in the trial after one year and roughly 60% completed three-years of follow-up^35^.

The percentage of women enrolled (40%) is slightly below the estimated prevalence in PD (42–46%)^36,37^ but is at the higher end of the 30–40% range typically enrolled in RCTs^38,39^, and is consistent with our clinic demographics, suggesting that sex representation in this trial reflects that of PD patients in the underlying clinic population.

The racial, ethnic, and sex composition observed here likely results from two main factors: 1) the pragmatic design, which reduced common participation barriers; and 2) the demographic profile of our clinic population^10,40^. Table 3 summarizes our study’s degree of pragmatism using the PRECIS-2 framework^23^.

**Table 3 Tab3:** Pragmatism of the trial design scored using the PRECIS-2 tool

PRECIS-2 Domain	Pragmatic Score range from 1 (very explanatory) to 5 (very pragmatic)	Description
Eligibility Criteria	5 (very pragmatic)	Anyone with PD or DLB psychosis likely to be a candidate for either medication in routine care
Recruitment	4 (rather pragmatic)	Usual appointments at diverse clinics, some advertising used
Setting	3 (equally pragmatic and explanatory)	Local academic center, multiple clinics, diverse socioeconomic backgrounds
Organization	4 (rather pragmatic)	No extra training for prescription management, 1:1 training for the trial protocol with the principal investigator, utilize extra research staff for record keeping and study management
Flexibility (Delivery)	5 (very pragmatic)	Medication prescribed per routine care at prescriber’s full discretion
Flexibility (Adherence)	5 (very pragmatic)	Medication managed per routine care
Follow-up	4 (rather pragmatic)	Mostly at routine appointments, some additional contact for outcome collection
Primary Outcome	4 (rather pragmatic)	NPI-Q not used in routine care, but is easily administered and targets psychosis severity
Primary Analysis	5 (very pragmatic)	Intention-to-treat using all available data

The broad eligibility criteria of our study enable nearly any patient with psychosis in PD or DLB to be considered for the trial, supporting more inclusive enrollment. Recruitment occurs during routine clinic visits with only limited outreach, keeping study activities closely aligned with usual care.

Financial costs, such as those incurred by travel, lodging, lost wages, or additional testing, have been recognized as major barriers to trial participation, particularly for patients from lower-income or underrepresented backgrounds^10,40^. In our study, assessments are scheduled during routine clinical 6-month follow-up visits, and data collection occurs alongside care with only minor extensions to visit length. This approach minimizes additional travel and time demands for patients and caregivers and thereby avoided burdens that often reduce retention^9,10^. Since both study arms use medications already prescribed in standard practice, no extra procedures or training were required for medication management, which also adds to the feasibility of the trial.

Language barriers are a known challenge to research participation^10^. At one major academic institution, a review of 1,492 studies showed that non-English speakers were ineligible to participate in almost half of the studies reviewed^41^. Our study sought to reduce this barrier by providing materials and consent forms in both English and Spanish, using bilingual staff, and arranging translators when necessary, allowing Spanish-speaking patients and families to participate fully.

The cohort’s mean SVM score is negative and the mean SVM percentile is lower than average, which indicates that participants on average are from less socially vulnerable areas^32^. However, the large standard deviation indicates a wide range of SVM scores among participants, with some living in higher-vulnerability communities. This supports the importance of maintaining accessibility features that lower participation burden across diverse socioeconomic backgrounds.

In addition, the outcome measures selected for this study reflect real-world considerations, including psychosis severity, medication adherence versus discontinuation, global impression of change, burden of neurology clinic care utilization, adverse events, and out of pocket treatment costs. Clinicians retain full discretion in treatment decisions, which adds to the practical relevance of results. Inclusion of caregiver burden as a key outcome recognizes the central role that families play when managing psychosis in LBDs. Together, these design elements align with proposed recommendations to address disparities in research^42^.

This study has several limitations. It is being conducted at a single academic center in a Hispanic majority city. While this helps improve representation among an often-underrepresented group, it may limit the generalizability of the results to other regions, healthcare settings, or demographic groups. Our study included only one Black participant, reflecting the clinic’s catchment population rather than differences in recruitment efforts. However, this highlights a broader challenge in neurology research, where Black patients remain consistently underrepresented. While pragmatic designs can lessen some logistical barriers, they cannot fully address structural inequities in access to specialty care or research participation. Future studies could strengthen partnerships with community organizations, expand outreach and trust-building, and ensure greater racial and cultural diversity among research and clinical teams to better address these inequities^10,42^. Centers with less diverse patient populations may consider collaborating with nearby institutions or community clinics to reach underrepresented groups in research.

The relatively modest sample size of the study reduces power for subgroup analyses and the ability to detect subtle differences between treatment groups. The open-label design introduces the possibility of bias, though this risk is mitigated by comparing two treatment arms receiving standard-of-care medications, without a placebo group. Treatment decisions, including dose adjustments and any changes in therapy, are made as part of routine care, which supports the pragmatic nature of the study but introduces variability that complicates precise comparisons between groups. Randomization stratification by center rather than by individual clinician may leave some residual influence from clinician practice patterns. Sensitivity analyses are planned to assess the extent of this effect.

Our findings support the feasibility of using a pragmatic trial design to evaluate antipsychotic treatments in LBDs. The study has achieved strong participant retention and successfully enrolled individuals from a historically underrepresented ethnic population. In doing so, it addresses pervasive challenges in neurodegenerative disease research regarding retention and representation. By reducing participation barriers and integrating research into routine care, pragmatic designs support more inclusive and patient-centered practices. Expanding such approaches in future studies may accelerate the application of evidence-based care, especially in underserved communities.

## Methods

### Study design and setting

This investigator-initiated, pragmatic, randomized, open-label clinical trial is being conducted at a single academic medical center in San Antonio, Texas. The trial compares the effectiveness and tolerability of quetiapine versus pimavanserin for the treatment of psychosis associated with Lewy body diseases, including PD and DLB. The study was registered on ClinicalTrials.gov, TRN: NCT05590637, Registration Date: 18 October 2022. This manuscript was prepared in accordance with the CONSORT 2025 statement and checklist (supplementary information)^43^.

The trial protocol was approved by the Institutional Review Board (IRB) at UTHSCSA (ID Number: 22-0198H) and is conducted in accordance with the Declaration of Helsinki and relevant regulatory requirements. Written informed consent is obtained from all participants or their legally authorized representatives prior to enrollment.

### Recruitment and enrollment

Participant recruitment began in 2022 and is paused for a planned interim analysis. Patients are identified through standard clinical workflows in neurology clinics. Eligibility screening and enrollment are performed during routine care encounters, and informed consent is obtained in person or remotely. No financial incentives are offered for participation. Both English- and Spanish-speaking patients are included. All study materials are available in both languages. Spanish-speaking participants are typically consented by bilingual clinicians or research staff, and certified interpreters are used when bilingual staff are unavailable, which is uncommon.

Eligible participants are adults with PD (including PDD) or DLB-related psychosis receiving care at the UTHSCSA or University Hospital Neurology Clinics (the latter is staffed by UTHSCSA Neurology faculty), for whom antipsychotic treatment is indicated. Diagnoses are made by movement disorders specialists during the course of routine clinical management. Clinical equipoise between quetiapine and pimavanserin must exist such that either medication is a reasonable treatment option, and the prescribing clinician must be comfortable prescribing and managing both. Patients meeting criteria are invited to participate by their clinician, who proceeds with enrollment or, if preferred by the clinician, involves a research coordinator to assist.

Exclusion criteria include any medical contraindication to either study medication, absence of a caregiver available to complete the Neuropsychiatric Inventory Questionnaire (NPI-Q)^44^, current use of an antipsychotic at the time of enrollment, or a prescribing clinician who is unwilling to manage both treatment options.

### Randomization and interventions

Participants are randomized in a 1:1 ratio to receive either quetiapine or pimavanserin. Seven clinicians participated in enrollment. Randomization is stratified by clinic site, performed using the NIH Clinical Trials Randomization Tool (https://ctrandomization.cancer.gov/tool/), and implemented using sequentially numbered, opaque, sealed envelopes. The allocated intervention is unblinded to all immediately after assignment. Consistent with the pragmatic design, clinicians retain full discretion in treatment decisions. All study medications are prescribed, managed, and adjusted as part of routine care by the treating clinicians, who do not have access to the random allocation sequence.

### Outcome measures

Outcomes are measured from baseline to six months (range: minus 2 weeks, plus 3 months). The primary outcome is the change in the combined NPI-Q hallucination and delusion item scores. Secondary outcomes include changes in the total NPI-Q score, clinician-rated Clinical Global Impression of Change (CGI-C), Patient Global Impression of Change (PGIC), Clinical Global Impression of Change for Caregiver Rating (CGI-C:CVR), time to discontinuation of the assigned medication, adverse events, mortality, change in the MDS-UPDRS Part III score^45^, and changes in other NPI-Q subdomains such as anxiety, agitation, and nighttime behaviors. A baseline formal cognitive assessment was not included, as study procedures were limited to measures that are quick and simple to obtain and most relevant to the study outcomes, in order to maintain pragmatism, minimize enrollment burden, and facilitate incorporation of study assessments into routine clinic visits. Planned exploratory outcomes include changes in the NPI-Q caregiver distress score, patient-reported out-of-pocket medication costs, and the frequency of patient contact with the neurology clinic, including visits, phone calls, and electronic medical record messages. Planned subgroup analyses include PD and DLB, Hispanic and non-Hispanic, and per-protocol treatment groups.

### Data collection and follow-up

Data are collected at baseline and again at the 6-month follow-up, which corresponds to a typical visit interval in our clinic, though some patients had additional visits during the trial period depending on clinical needs. In-person visits are preferred, though telemedicine visits are permitted. Data collected during visits include patient and caregiver interviews, medication records, and standardized assessments. Each visit is extended approximately five additional minutes to complete the consent process, randomization, and outcome measures. The NPI-Q is typically completed by the caregiver while other clinical activities, such as the neurological exam or prescription management, are underway. If caregivers are not physically present, the clinician or a research coordinator can collect the NPI-Q data by phone. Patients who do not return for an in-person visit during the follow-up period are contacted by phone to obtain outcome data. For phone or telemedicine follow-ups, the motor examination (MDS-UPDRS Part III) is not performed. Treating clinicians were individually trained by the principal investigator (PI) on the study protocol and assessments. A research coordinator trained in the study is available to assist upon request. The PI oversees data quality throughout the study. Some data are extracted from the electronic medical record (EMR) by the research team, including race and ethnicity, which are reported by participants and recorded in the EMR.

### Demographics comparison

The overall cohort of PwP included all patients seen in the UTHSCSA Neurology Clinic with an International Classification of Disease (ICD-10) code for PD. Electronic medical records were reviewed for PD diagnosis confirmation, and PwP were included in this cohort if they first saw a movement disorders specialist at UTHSCSA between 2014, when the Movement Disorders Clinic was established, and 2022, when the cohort was created.

The pragmatic trial cohort is compared with participants enrolled in concurrent explanatory RCTs for people with PD and/or DLB within the Movement Disorders Division at our center. Participants are considered retained if they enrolled in the study and have either completed the study or remain in the study, as opposed to those who screen failed, terminated the study early, or died.

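### The retention definition counts screen failures as losses, so 93% versus 40% is not shown to be a like-for-like measure of retention after randomisation

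*Protocol article*

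**What the plan says.** The abstract states that "retention is higher (93% vs 40"%, p < 0.001, and the results paragraph before Table 2 repeats this. The definition is in the methods, under Demographics comparison. It counts completers and those still active as retained, and it names three ways of not being retained: "as opposed to those who screen failed, terminated the study early, or died".

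For the pragmatic trial, the main text reports "a total of 56 participants are enrolled and retained (93%), including 48 who have completed the study and 8 who remain active". The denominator is the randomised set: "Thirty (50%) were randomized to receive pimavanserin and 30 (50%) to quetiapine". The losses are itemised: "Four participants were lost to follow-up (2 due to death and 2 due to relocation or withdrawal"). Under Recruitment and enrollment, "Eligibility screening and enrollment are performed during routine care encounters", and it is patients who meet the criteria who are then invited by their clinician.

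The comparison group is described as participants enrolled in "concurrent explanatory RCTs for people with PD and/or DLB within the Movement Disorders Division at our center (*n* = 68"). The article does not split those not retained in this group into screen failures, early terminations and deaths.

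**The concern.** Retention normally describes what happens after a person has entered a trial. Here the definition puts a screening outcome into the same category as early termination and death. In the pragmatic trial, eligibility is settled at a clinic visit before the invitation, and everyone in the denominator was randomised. The screen-failure clause therefore removes nobody from its numerator. In the explanatory trials, naming screen failure as a way of not being retained implies that the 68 can include people who consented but were never randomised.

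The two percentages may therefore start from different points: randomisation in one group, and entry to screening in the other. At stake is the article's lead result, which the abstract uses to support the message that embedding trials in routine care can improve retention. If part of the 54-point gap comes from screening, that part says nothing about whether participants stay once they are in.

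**Working it through.** **Inputs.** Pragmatic trial: 60 randomised, 56 retained (48 completed + 8 active), 4 lost, 0 of them screen failures (main text). Explanatory trials: n = 68, 40% retained (results paragraph before Table 2). Test: chi-squared (Statistical analysis). No significance level is stated for this comparison, so 0.05 is assumed.

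**Recovering the explanatory count.** 26/68 = 38.2%, 27/68 = 39.7% and 28/68 = 41.2%. Only 27 rounds to 40%, so 27 were retained and 68 − 27 = 41 were not.

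**Reproducing the published result.** 56/60 = 93.3% against 27/68 = 39.7%. Pearson chi-squared = 128 × (56×41 − 4×27)² / (60 × 68 × 83 × 45) = 40.2, p = 2.3 × 10⁻¹⁰ (continuity-corrected 7.5 × 10⁻¹⁰; Fisher exact 5.4 × 10⁻¹¹). This agrees with the stated 93% versus 40%, p < 0.001.

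**Removing screen failures.** Let s be the number of screen failures among the 41. The article does not give s, so the whole range from 0 to 41 is open. Holding the 27 retained fixed, explanatory retention becomes 27/(68 − s), tested against 56/60:

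| s | Explanatory retention | Gap to 93.3% (points) | Pearson p |
|---|---|---|---|
| 0 | 27/68 = 39.7% | 53.6 | 2.3 × 10⁻¹⁰ |
| 10 | 27/58 = 46.6% | 46.8 | 2.7 × 10⁻⁸ |
| 20 | 27/48 = 56.3% | 37.1 | 5.6 × 10⁻⁶ |
| 28 | 27/40 = 67.5% | 25.8 | 0.0008 |
| 30 | 27/38 = 71.1% | 22.3 | 0.003 |
| 34 | 27/34 = 79.4% | 13.9 | 0.044 |
| 35 | 27/33 = 81.8% | 11.5 | 0.086 |
| 39 | 27/29 = 93.1% | 0.2 | 0.97 |

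**Thresholds.** By Pearson chi-squared, p stays below 0.001 up to s = 28 and below 0.05 up to s = 34. Losing significance needs at least 35 of the 41 (85%) to be screen failures, and near parity needs 39 of 41 (95%). Fisher's exact test crosses 0.05 one step earlier: p = 0.029 at s = 33 and 0.091 at s = 34.

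**Still-active participants.** Restricting the pragmatic trial to those with a final status gives 48/(48 + 4) = 48/52 = 92.3%, against 93.3% as reported.

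**The case against.** A reader might infer that the definition produces the headline result. The article does not support that. The number of screen failures appears nowhere, and because the comparison group is called enrolled, it could be zero. Over most of the possible range the difference stays far from the 0.05 boundary. This part of the objection stands.

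The definition is also worded for both groups. That it can lower only the explanatory figure is read from the reported counts and the enrolment process, not from the wording. The inference is sound for the data shown, since all 60 were randomised and the 4 losses are accounted for.

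A reader might also infer that counting the 8 active participants as retained inflates the result. For this trial the effect is about one percentage point. The same rule applies to the explanatory trials, where it would raise the 40%. No direction of bias is shown.

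Finally, this is a descriptive, non-randomised comparison with an openly stated definition. It does not touch the randomised comparison, the primary outcome, the sample size or the interim analysis. The closing paragraph claims only strong retention, which 56/60 supports on its own, and the discussion also places the 93% beside another pragmatic PD trial with 91% at one year. All of this limits the weight of the point. It does not make the two percentages comparable: a p-value that survives is no answer when the printed contrast of 54 points could be 37 or 22.

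**Conclusion.** The point holds as a defect of definition in a reported headline comparison. Screen failure is counted as non-retention, and in the reported data this can pull down only the explanatory figure. The 93% versus 40% is therefore not shown to compare retention after randomisation in both groups. Explanatory retention on that basis could be anywhere from 40% (no screen failures) upward, reaching 93% at 39 screen failures. The difference may well stay significant, but its size cannot be determined from the article.

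This rests on three assumptions: 27 retained among the 68, as the rounding forces; that those 27 stay the same when screen failures are removed; and a 0.05 level for the thresholds. The point is of moderate weight. It affects how the comparison is presented, not the trial's treatment analysis.

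**What to change.** 1. Under Demographics comparison, define retention from randomisation in both groups and take screen failures out of the denominator.
2. Report screen failures separately as a screening outcome.
3. Break the 41 non-retained explanatory participants down into screen failure, early termination and death.
4. Restate the 93% versus 40% comparison and its p-value in the abstract and in the results paragraph before Table 2 with the like-for-like figures. The closing paragraph does not carry this comparison and needs no change on this account.

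A time-to-event estimate of retention with active participants censored would be an optional addition. The article gives no durations for the explanatory trials, so its suitability cannot be checked here.

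The cost is recoding 68 local records, with no change to any trial procedure. The contrast may become less favourable. If few of the 41 were screen failures, it will change little and be better supported.

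### The retention rule counts screen failures as not retained, so the 40% for the explanatory RCTs may include screening loss while the 93% for the pragmatic trial covers only randomized participants

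*Protocol article*

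**What the plan says.** The Demographics comparison section of the Methods gives one rule for both groups. A participant is retained if enrolled and either finished or still in the study, "as opposed to those who screen failed, terminated the study early, or died".

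The main text, which runs on under the Abstract heading, gives the pragmatic trial's count: "a total of 56 participants are enrolled and retained (93%), including 48 who have completed the study and 8 who remain active". The losses are itemised: "Four participants were lost to follow-up (2 due to death and 2 due to relocation or withdrawal"). The denominator of 60 is fully randomized: "Thirty (50%) were randomized to receive pimavanserin and 30 (50%) to quetiapine".

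The comparison group is the set of participants in concurrent explanatory RCTs "within the Movement Disorders Division at our center (*n* = 68"). Against that group the pragmatic trial "demonstrated improved retention (93% vs 40"%), with p < 0.001. The article does not say why the other RCT participants were not retained.

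Two sections describe how people enter the pragmatic trial. Recruitment and enrollment states: "Eligibility screening and enrollment are performed during routine care encounters, and informed consent is obtained in person or remotely". Data collection and follow-up states: "Each visit is extended approximately five additional minutes to complete the consent process, randomization, and outcome measures". Neither describes a separate screening period between consent and randomization.

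**The concern.** Retention asks whether people who start follow-up stay in it. Screening loss reflects how strict eligibility is and where consent falls relative to the eligibility checks. The rule puts both into one non-retained class. On the reported counts, screening loss adds nothing to the pragmatic trial's non-retained group, but it may add to that of the explanatory RCTs. The two percentages may then start from different points: randomization in one, an earlier point in the other.

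At stake are the size and meaning of the first result in the abstract. The abstract concludes from it that embedding trials in routine care can improve retention, and the discussion links this to lower travel and time demands. That argument is about staying in a trial. A figure that includes screening loss does not measure it cleanly.

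**Working it through.** **Inputs.** Pragmatic trial: 56 retained of 60; losses 2 deaths + 2 relocation or withdrawal = 4 (main text). Explanatory RCTs: 40% of 68 (main text). Test: chi-squared (Statistical analysis); the article does not say whether a continuity correction was used.

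**Step 1: reproduce the stated figures.**
- 56/60 = 93.3%.
- For n = 68, only 27 retained rounds to 40% (26/68 = 38.2%, 27/68 = 39.7%, 28/68 = 41.2%). So 27 were retained and 68 − 27 = 41 were not.
- Gap: 93.3 − 39.7 = 53.6 points (53 from the rounded percentages).
- Uncorrected chi-squared = 128 × (56×41 − 4×27)² / (60×68×83×45) = 40.2, p = 2 × 10⁻¹⁰. With continuity correction p = 7 × 10⁻¹⁰. Both agree with p < 0.001.

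**Step 2: screen failures in the pragmatic figure.** The 60 are 30 + 30 randomized, and the four losses are all accounted for by death, relocation or withdrawal. The count among the 60 is zero.

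**Step 3: remove screen failures from the RCT denominator.** Let s be the number of screen failures among the 41. Retention without them is 27/(68 − s). The article does not give s, so the values below are assumptions that show the range. The 95% CI is the simple (Wald) interval, difference ± 1.96 × √[p₁(1−p₁)/60 + p₂(1−p₂)/(68−s)].

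| s (assumed) | RCT retention | Gap, points | 95% CI | p, uncorrected |
|---|---|---|---|---|
| 0 | 27/68 = 39.7% | 53.6 | 40 to 67 | 2 × 10⁻¹⁰ |
| 10 | 27/58 = 46.6% | 46.8 | 32 to 61 | 3 × 10⁻⁸ |
| 20 | 27/48 = 56.3% | 37.1 | 22 to 52 | 6 × 10⁻⁶ |
| 30 | 27/38 = 71.1% | 22.3 | 7 to 38 | 0.003 |
| 34 | 27/34 = 79.4% | 13.9 | – | 0.044 |
| 35 | 27/33 = 81.8% | 11.5 | – | 0.086 |
| 39 | 27/29 = 93.1% | 0.2 | – | 0.97 |

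**Step 4: limits for significance.** Uncorrected, p stays below 0.001 up to s = 28 and below 0.05 up to s = 34. With continuity correction the limits are 26 and 33.

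Every screen failure removed raises the RCT percentage, so the direction is fixed once s is at least 1. The amount is not.

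**The case against.** The strongest reply is that the decisive count is missing. The article calls the 68 enrolled participants and does not describe how those RCTs screen. The mention of screen failure could be generic wording that applied to nobody. This stands as a limit: the overstatement is conditional on s ≥ 1. But no pragmatic-trial loss was a screen failure, so the category has a use in this comparison only if it applied to the RCTs.

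Second, a single disclosed rule was applied to both groups, and loss at screening could be seen as part of a broader completion measure. That is fair, but the result is labelled retention and explained by participation burden. A broader measure would also need the pragmatic trial counted from the same earlier point, and the article gives no such count.

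Third, the qualitative result is robust, as Step 4 shows, and the article also cites published retention figures, including 91% at one year in another pragmatic PD trial. This stands, and it limits the point to the size of the contrast.

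A reader might also infer more than the documents support:
- **That the pragmatic trial could not have screen failures after consent.** The entry process suggests this, but the article does not rule it out. It shows only that there were none among the 60.
- **That the RCT denominator is known to be everyone who consented.** The article does not say so.
- **That the definition contradicts itself.** It does not. Screen failure is the counterpart of the enrolled condition; early termination and death are the counterparts of completing or remaining. The tension is only with the preceding sentence, which describes the comparators as enrolled.
- **That some RCT losses were trials closed by their sponsors.** The article mentions no such closures.

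**Conclusion.** The point holds as a defect in a stated rule that has already been used for a headline figure. The 93% is retention after randomization, while the 40% can include people lost at screening. If any of the 41 were screen failures, the gap of about 53 points overstates the retention difference. The overstatement cannot be computed from the article. Assumed counts of 10 to 30 leave a gap of 47 to 22 points.

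It would go too far to conclude that the retention advantage is an artefact. That would need about 35 or more of the 41 to be screen failures before significance at 0.05 is lost (34 with continuity correction), and about 39 before the gap closes. Nothing in the article points to such a split. The conclusion rests on 27/68 as the only count that rounds to 40%, and on the reported breakdown of the 60. The randomization, primary outcome, sample size and treatment comparison are untouched.

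**What to change.** Define retention in both groups as (completed or still in follow-up) / randomized. Report screen failures in a separate row, outside that denominator. Split the 41 RCT participants not retained into screen failure, early termination and death. Restate both percentages, the difference with a 95% CI and the p-value in the abstract and main text. If none of the 41 was a screen failure, one sentence saying so settles the matter and the figures stand.

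The cost is a re-tabulation of records that have already been classified for this comparison. The only downside is a contrast that may turn out less favourable.
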